## Abstract

**Background:**

Radiation dermatitis (RD) is the most common side effect of breast irradiation, yet only few potent preventative and therapeutic options are available. Following encouraging results from a phase 1 and 2 trial on the topical use of non-invasive physical plasma (NIPP), a very well-tolerated physical treatment option to promote tissue regeneration generated from ambient air, we now present the study protocol for a planned phase 3 trial.

**Methods:**

In this randomised double-blind placebo-controlled trial, patients with breast cancer will be randomised (1:1) to receive either 120 s of NIPP or sham treatment with an identical device daily during hypofractionated breast irradiation following breast-conserving surgery. Standard skin care with urea lotion will be applied twice daily to the whole breast by all patients. Acute skin toxicity will be assessed weekly and includes clinician- (CTCAE v5.0) and patient-reported (modified RISRAS), and objective (spectrophotometry) assessments. The trial has started enrolment in the first quarter of 2024 and is projected to recruit 140 patients over 36 months.

**Discussion:**

This randomised controlled trial will recruit a homogeneous patient collective in terms of RD risk and aims to unequivocally establish the impact of NIPP on RD by employing a robust trial design, incorporating both the patient’s perspective and validated objective outcome measures. If the addition of NIPP proves useful, it might reduce both physical and psychological distress caused by RD in numerous breast cancer patients and beyond.

**Trial registration:**

German Clinical Trial Registry DRKS00032560 (January 9th 2024).

## Administrative information

The numbers in curly brackets in this protocol refer to SPIRIT checklist item numbers. The order of the items has been modified to group similar items (see http://www.equator-network.org/reporting-guidelines/spirit-2013-statement-defining-standard-protocol-items-for-clinical-trials/).

Role of Sponsor {5c}	The sponsor and funding body have no role in the design of the study, in collection, analysis, and interpretation of the data or in the writing of the manuscript.

## Introduction

### Background and rationale {6a}

Early breast cancer remains the most common oncological diagnosis [1]. Treatment usually involves lumpectomy followed by adjuvant breast irradiation to improve local control and (in most cases) survival [2]. Radiation dermatitis (RD), characterised by erythema, pruritus, discomfort, and dry or moist desquamation, is the most common acute side effect of breast irradiation, occurring in up to 85% of patients [3, 4]. Although severe cases have become rare following advancements in radiation treatment technique and the exploration of new fractionation regimens, even moderate or mild symptoms are known to impact quality of life and self-image [5, 6]. Potent preventative and therapeutic options remain limited and due to insufficient and sometimes even conflicting evidence, recommendations can currently only be made for a handful of interventions, resulting in substantial variations in RD management amongst practitioners and institutions [7–11].

Non-invasive physical plasma (NIPP) is an effective treatment modality for several skin conditions, including psoriasis, eczema, diabetic ulcers, and different types of dermatitis [12, 13]. Physical plasma can be regarded as the fourth state of matter and is a highly energetic, partially ionised gas characterised by free electrons [14, 15]. NIPP is created using a high-frequency alternating field under atmospheric pressure, therefore only reaching room temperatures and making it safe for clinical application. Dielectric barrier discharges (DBDs) are a type of NIPP, generated out of ambient air, omitting the need for a carrier gas [16]. Several trials have demonstrated that this reactive mix of electrons, ions, excited atoms, and reactive oxygen and nitrogen species (RONS) positively affects tissue healing in a dose-dependent manner [17]. NIPP treatment is well-tolerated with multiple trials confirming its safety and thus far complete absence of side effects [13, 18–20].

Recent evidence has identified the skin microbiome as a risk factor for (severe) RD, postulating the hypothesis that bacterial decolonisation might be an effective prophylactic approach, which would be the main mode of action of NIPP in this context [21–23]. Furthermore, NIPP promotes proliferation and migration of keratinocytes, fibroblasts, and endothelial cells, thus facilitating tissue regeneration [24]. The expression of wound healing gene signatures alongside significant changes to the human skin barrier lipid stoichiometry are two additional modes of action, which are thought to positively impact the complex pathophysiology of RD [25, 26]. In an investigator-initiated first-in-human phase 1 benchmarking trial (*n* = 30), we previously reported safety and feasibility features of a topical DBD-generated NIPP-based prevention of acute RD [27]. In the follow-up phase 2 trial (*n* = 64), we established the preliminary efficacy of this approach, with a positive impact on both clinician- and patient-reported endpoints [28]. As expected, tolerability of NIPP was excellent and no side effects occurred.

### Objectives {7} and trial design {8}

In this current prospective phase 3 randomised double-blind placebo-controlled trial, we aim to establish the effects of add-on NIPP on the incidence and severity of RD and associated symptoms in patients undergoing breast irradiation, with clinician-assessed RD (as per CTCAE v5.0) upon radiation treatment completion as the primary endpoint.

## Methods

### Study setting {9}

Patients will be recruited by the Department of Radiation Oncology at the University Hospital Bonn in Germany, upon referral from the Department of Gynaecology and Gynaecological Oncology, Division of Senology, after multidisciplinary recommendation of adjuvant breast irradiation in the joint interdisciplinary tumour board.

### Eligibility criteria {10}

#### Inclusion criteria

Strict inclusion and exclusion criteria are defined to ensure a homogeneous patient collective. All patients with invasive breast cancer (ICD-10 C50.9) or ductal carcinoma in situ (ICD-10 D05.10) scheduled for adjuvant breast irradiation following breast-conserving surgery (i.e. lumpectomy) will be screened. The following inclusion criteria apply:* Age ≥ 18 years (no upper limit);* Moderately hypofractionated radiation regimen in 15 fractions, with at least a whole-breast target volume and with or without a boost to the tumour bed (either simultaneous integrated or sequential);* Oral and written informed consent.

#### Exclusion criteria

To omit bias in RD development and grading, subjects will not be included if any of the following exclusion criteria applies:* Synchronous metastatic disease;* Mastectomy;* Reconstruction with breast implant;* Prior skin infiltration by tumour necessitating the use of a bolus;* Impaired surgical wound healing at the time of radiation treatment initiation;* Alternative fractionation regimens;* History of ipsilateral breast irradiation;* Any pre-existing dermatological disorder;* Active dermatitis;* Current treatment with topical or oral corticosteroids;* Patient refusal to participate;* Subjects without legal capacity to understand the nature, scope, significance, or consequences of a clinical trial.

### Informed consent {26a} {26b}

Informed consent will be obtained by specifically trained radiation oncologists registered as investigators for the trial.

## Interventions

### Explanation for the choice of comparators {6b}

Both the previous phase 1 and 2 trial have demonstrated preliminary efficacy of NIPP in the context of RD prevention during breast irradiation [27, 28]. NIPP will be investigated as an add-on modality to standard skin care with a moisturising lotion.

### Intervention description {11a}

#### Radiation treatment

All patients will receive 36 − 40.05 Gy in 15 fractions of 2.4 − 2.67 Gy each to the whole breast and 40.05 Gy in 15 fractions of 2.67 Gy each to the partial breast. Patients ≤ 50 years or those with established risk factors (≥ pT2, HER2 positive, triple-negative, or poor cell differentiation) will receive either a simultaneous integrated (48 Gy in 15 fractions of 3.2 Gy each) or sequential boost (10 − 16 Gy in 5 − 8 fractions of 2 Gy each) to the tumour bed (choice at the discretion of the treating radiation oncologist and patient). Target volume delineation will follow international standards [29–31]: the whole-breast clinical target volume (CTV) will be defined as all residual ipsilateral glandular breast tissue, whereas the partial-breast CTV will be delineated as the lumpectomy cavity (including surgical clips and postoperative seroma), radially expanded by 1 − 1.5 cm. Both CTV and planning target volume (PTV) will be cropped 5 mm from the skin surface. Treatment technique will be photon-based 6 MV sliding window intensity-modulated radiotherapy (IMRT), hybrid 6 and 10 MV volumetric modulated (partial) arc therapy, or electronic tissue compensation (eComp). Planning will aim for a homogeneous dose distribution while avoiding hotspots in the skin region and following the International Commission on Radiation Units and Measurements (ICRU) recommendations for dose limits of 95–107%. All patients will be treated on a TrueBeam STx (Varian Medical Systems, Palo Alto, CA, USA) linear accelerator in a supine position on a breast board. Left-sided breast irradiation will be performed in deep inspiration breath-hold (DIBH) for compliant patients. The irradiated breast skin will be defined as the 5 mm layer between the body contour and the radially expanded (1.5 cm) whole-breast PTV. Breast skin dose will be assessed dosimetrically (e.g. V_107%_) to ensure balance between groups.

#### Standard skin care

Institutional standard skin care with urea-based lotion (UreaRepair PLUS 5%, Eucerin, Beiersdorf, Hamburg, Germany) will be applied twice daily to the whole breast from the first day of treatment onwards until 4 weeks after radiotherapy completion. All patients will be provided with oral and written instructions alongside information on general skin care during radiotherapy (e.g. washing with mild soap, drying with a soft towel, deodorant use).

#### Non-invasive physical plasma

Several NIPP-generating devices are commercially available. The device used in this trial will be plasma care (terraplasma medical, Garching, Germany). This wireless, handheld, class 1 medical device is certified for use in the context of dermatological disorders, specifically for prophylaxis and therapy of inflammatory skin diseases caused by ionising radiation. In this setting, it can also explicitly be used as an add-on to standard skin care. The device is used with a separate sterile spacer with a 4 × 4 cm NIPP contact surface. For each patient and each visit, the device is then pressed loosely onto the patient’s breast skin, ensuring that the distance to the skin is always kept the same (Fig. 1). The application will be repeated in each of the breast quadrants. Based on the initial feasibility and dose-escalation trial, the daily treatment time is set at 120 s, using the device’s preset programme to ensure a constant dose of NIPP [27]. NIPP will be applied daily by a trained radiation oncology nurse, following every radiation fraction.

**Fig. 1 Fig1:**
[figure not shown]
Generation and application of NIPP on the breast skin. The device is pressed loosely on the skin with a separate 4 × 4 cm spacer for each patient and each visit. NIPP = non-invasive physical plasma. Image from [name] et al. [27], with permission

#### Placebo

Patients randomised to the control arm will receive sham treatment with an identical device, which produces the same sound and feeling, yet does not produce NIPP. To keep the devices separated, they will be marked “1” and “2”. The treating radiation oncology nurse is the only one who will be aware of the exact allocation.

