#### Assignment of interventions: allocation

### Sequence generation {16a}

Using intrapatient randomisation (the irradiated breast is divided into a lateral and medial half; one breast half receives experimental treatment, while the other breast half receives standard of care or placebo) has proven useful in several trials investigating (acute or chronic) RD management approaches [37–40]. This omits the need for stratification based on known risk factors influencing the RD risk and limits confounding when assessing trial endpoints. The volatile nature of NIPP, however, does not allow such trial design, as potential diffusion to the contralateral (placebo) breast half with a subsequent effect is likely, as was the case in our phase 2 trial [28]. Therefore, a separate control group receiving standard skin care + placebo will be recruited. A 1:1 randomisation (NIPP:placebo) will be undertaken, with patient stratification based on two proven risk factors for RD development and severity: total radiation dose (i.e. presence or absence of a boost to the tumour bed) and irradiated breast volume (as measured in the radiation treatment planning computer tomography: small < 400 mL, medium 400 − 800 mL, large > 800 mL) [35, 41]. Patients will be assigned to intervention or placebo using a stratified block randomisation process (block size will be disclosed upon final publication of the results), using a computer-generated random number list, created by a team member not involved in the clinical part of the trial. Other factors which are known to modulate the RD risk (e.g. body mass index, diabetes mellitus, smoking history, Fitzpatrick skin type) will not be included in the stratification process, but will be documented and presented (including balance between groups).

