### Concealment mechanism and implementation {16b} {16bc}

Allocation will be undertaken by a trained radiation oncology nurse who is also the NIPP/placebo device operator. Allocation information will be stored on a password-protected secure server, inaccessible to the blinded investigators.

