## Assignment of interventions: blinding

### Who will be blinded? {17a}

Patients and treating physicians will be blinded until completion of the trial for individual patients; only the device operator is aware of the respective allocation and will not be conducting any assessments. Data analysts and statisticians will also be blinded.

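### The device operator knows which device is active although a code would be enough to deliver treatment: a cheap improvement that mainly protects the patient-reported outcomes

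*Protocol article*

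**What the plan says.** The Placebo section describes the control as "sham treatment with an identical device, which produces the same sound and feeling, yet does not produce NIPP". The devices are told apart by the neutral marks 1 and 2. The same section then says: "The treating radiation oncology nurse is the only one who will be aware of the exact allocation".

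Four other sections define what that role does:

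- **Delivery** (Non-invasive physical plasma): "NIPP will be applied daily by a trained radiation oncology nurse, following every radiation fraction".
- **Allocation** (Concealment mechanism and implementation): "Allocation will be undertaken by a trained radiation oncology nurse who is also the NIPP/placebo device operator". The allocation data are held on a protected server that the blinded investigators cannot reach.
- **Blinding** (Who will be blinded?): patients, treating physicians, data analysts and statisticians are blinded, while "only the device operator is aware of the respective allocation and will not be conducting any assessments".
- **Disclosure** (Procedure for unblinding): once an individual patient has completed the trial, the treating nurse reveals the arm if the patient asks. Sealed envelopes cover emergencies.

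The section on the coordinating center and steering committee speaks of unblinded study nurses in the plural, so more than one person may hold the key. Sequence generation says that the randomisation list is "created by a team member not involved in the clinical part of the trial".

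**The concern.** Four functions sit in one role: allocating, treating, knowing the key and disclosing it. On the protocol's own description of the sham, the operator needs none of that knowledge to deliver treatment. In many device trials operator unblinding cannot be avoided. Here it appears to be a choice, and no reason is given for it.

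The operator sees each patient after every fraction. Someone who knows the arm can, without intending to, reassure one patient more than another, or let a remark drop to the patient or to a colleague. Keeping the operator out of assessments deals with how outcomes are graded, but not with what patients come to believe or report. At stake is the credibility of the outcomes that depend on patient expectation, in a trial that wants to settle whether the treatment works.

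**Working it through.** The point rests on no figure in the plan, so the check sets the sections side by side.

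**1. Is the key needed to deliver treatment?** The operator needs to know which device to pick up and how to apply it. The device mark supplies the first. The device's preset programme and a constant distance to the skin (Non-invasive physical plasma) supply the second. The sham is one "which produces the same sound and feeling, yet does not produce NIPP". Nothing in the procedure depends on knowing which number is active.

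**2. Could someone else hold the key?** Yes. Sequence generation already provides a non-clinical list creator.

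**3. Which outcomes do the existing safeguards cover?**

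| Outcome | Safeguard in the article | Route left open |
|---|---|---|
| CTCAE grade (primary) | Blinded oncologist makes all clinical assessments; operator makes none | Indirect only: cues to colleagues or differences in care |
| Spectrophotometry | Automatic readings | Little |
| Modified RISRAS | Patient blinded | What the operator conveys to the patient |
| Corticosteroid prescription rate | Prescriber blinded | Patient complaints shaped by expectation, or cues to the prescriber |
| Lotion use | Same oral and written instructions for all; compliance checked by the treating oncologist | Informal encouragement |

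**4. Would a code alone hold with only two numbers?** Not reliably. Patients may learn their arm as they finish, while others are still being treated. With two fixed numbers, one disclosed arm linked to its number identifies that device, and the other by elimination. In principle this settles the arm of all 168 randomised patients (Sample size). So the remedy needs either more codes or later disclosure.

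**5. Size.** The documents give no estimate of any bias, so none can be derived. As an illustration only, take the primary grade with SD 0.7 and 70 per arm (Sample size), no true effect, and an *assumed* spurious arm difference b. In a normal approximation, the shift of the test statistic is δ = (b / 0.7) × √(70/2), and the two-sided error rate is 1 − Φ(1.96 − δ) + Φ(−1.96 − δ).

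| Assumed b (grade) | δ | Error rate |
|---|---|---|
| 0 | 0 | 5.0% |
| 0.05 | 0.42 | 7.1% |
| 0.10 | 0.85 | 13.5% |
| 0.20 | 1.69 | 39.4% |

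This shows how sensitive a comparison of this size would be to a one-directional bias. It is not evidence that such a bias occurs. The planned Mann–Whitney-Wilcoxon test would behave somewhat differently, and the CTCAE grade is the better-protected outcome. No matching calculation is possible for RISRAS, because the article gives no standard deviation for it.

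**The case against.** The strongest reply is that the protocol discloses this arrangement openly and surrounds it with safeguards: a blinded assessor, a non-assessing operator, blinded analysts, a server closed to investigators, uniform skin-care instructions, compliance checks by a blinded physician, a fixed device programme and automatic colour readings. Careless or careful application of a sham that emits no plasma cannot change its dose. Rules on what staff may say could sit in the full protocol or a trial manual. A trained operator might also tell the devices apart by cues other than sound and feel. Most of this stands. It narrows the concern to conversational influence, but it does not explain why the operator should hold the key.

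Three stronger readings are tempting, and the document does not support them:

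- **That the double-blind label is contradicted.** The blinding section lists who is blinded and says plainly that the operator is not. The term is used consistently with that list.
- **That knowledge of earlier assignments in a block lets enrolment be steered.** Investigators, not nurses, recruit and enrol, and they cannot see the allocations. Selection bias would require a leak from nurse to investigator, which nothing in the article suggests.
- **That the number of treatment sessions measures the harm.** Counting contacts shows opportunity, not bias.

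**Conclusion.** The point holds as a low-cost improvement. One or more nurses know which device is active when, on the protocol's own description of the sham, a device code would do. The primary CTCAE grade and the spectrophotometry are largely protected. The residual risk falls mainly on the modified RISRAS and the corticosteroid prescription rate, and only indirectly on the CTCAE grade.

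The size of that risk is unknown, and nothing indicates that bias has occurred. A reader might infer that the primary result would be unreliable as planned; with a separate blinded assessor in place, the document does not support that. The conclusion rests on two assumptions: that the sham matches the active device as closely as described, and that the full protocol gives no operational reason for the operator to know the key.

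**What to change.** Amend the Placebo, Concealment, Who will be blinded and Procedure for unblinding sections as follows:

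- The operator receives only a device code for each patient. The active/sham key stays with the list creator.
- Devices are re-labelled, so that what the nurses now know becomes void.
- Either more than two codes are used, so that one disclosed arm does not identify all other patients, or routine disclosure to patients waits until the last patient has completed.
- Any routine disclosure is made by the key holder and not by the nurse.
- The sealed emergency envelopes stay as they are.

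**Cost.** A short amendment through the route the protocol already sets out, plus relabelling. Patients would learn their arm later or less directly. More codes may mean more devices or repeated relabelling, whereas deferring disclosure needs neither; the article does not say how many devices are available. The operator may still sometimes guess the arm, so the change reduces the risk without removing it. Patients already treated are unaffected; the benefit is to those still to be treated.

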### Criteria for discontinuing or modifying allocated interventions {11b}

At the discretion of the investigators, patients presenting with grade ≥ 2 RD, moist desquamation, or intense pain can be prescribed topical corticosteroids (methylprednisolone aceponate) until symptoms resolve. Any medication prescribed for local symptoms will be documented regarding dose, duration, and mode of application. Patients can withdraw informed consent at any point in time. If so, the reason(s) will be documented. Cross-over between arms is not planned.

### Strategies to improve adherence to interventions {11c}

Compliance with standard skin care will be checked by the treating radiation oncologist during the scheduled patient visits.

